### Randomization

Eligible participants will be randomly assigned to the ICBT or UC group at a ratio of 1:1, with assignments made using the minimization method, ensuring a balance in baseline Y-BOCS scores (Y-BOCS ≥20) and gender.

### Statistical Analysis Plan

Statistical analysis and reporting will be conducted in accordance with CONSORT (Consolidated Standards of Reporting Trials) guidelines [38], with primary analyses based on the intention-to-treat principle. For baseline variables, summary statistics will be constructed, employing frequencies and proportions for categorical data and mean and SD for continuous variables. Baseline variables will be compared using the Fisher exact test for categorical outcomes and the unpaired *t*-test for continuous variables. For the primary analysis comparing treatment effects, the least-squares means and their 95% CIs will be estimated by analysis of covariance (ANCOVA) with the change in total Y-BOCS scores at week 12. This ANCOVA model will account for the variation caused by treatment effects, and gender and baseline Y-BOCS scores will be entered as covariates. Analyses of secondary outcomes will be performed in the same manner. All comparisons are planned, and all *P* values will be two-sided. *P* values <.05 will be considered statistically significant. All statistical analyses will be performed using the latest version of SAS (SAS Institute Inc).

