**Methods:**

The randomized controlled trial will compare internet-based cognitive behavioral therapy treatment and usual care groups, each consisting of 15 participants (n=30) diagnosed with obsessive-compulsive disorder. We will evaluate the effectiveness of a 12-week intervention. The primary outcome of symptom severity will be measured using the Yale-Brown Obsessive-Compulsive Scale. Secondary outcomes will be assessed with the Obsessive-Compulsive Inventory, Beck Anxiety Inventory, Patient Health Questionnaire-9, Generalized Anxiety Disorder-7, Working Alliance Inventory-Short Form, and the Euro Qol – 5 Dimension. All measures will be assessed at weeks 0 (baseline) and 12 (follow-up). In the statistical analysis comparing treatment effects, the least-squares means and their 95% CIs will be estimated by analysis of covariance with the change in total outcomes scores at week 12. All comparisons are planned, and all *P* values will be two-sided, with values <.05 considered statistically significant.

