### Sample Size

We used the statistical analysis software G*power 3.1 to estimate sample size of an unmatched t-test [37]. Sample size was estimated as 14 participants per group. The effect size predicted in this study is at least 1.00 from the two previous two clinical trials [8-10], the directionality of the test is a two-sided test, the significance level was set at 0.05%, the test was two-sided, and the test power (1-β) was set to 80%. The study will require a minimum 14 participants per group so we are setting a target enrollment of 30 participants to allow for a 5% dropout rate.

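### The plan should state which baseline adjusts each secondary outcome: it names only gender and baseline Y-BOCS and carries that model over

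*Protocol article*

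**What the plan says.** In the protocol article, the Statistical Analysis Plan section says that treatment effects on the primary outcome will be "estimated by analysis of covariance (ANCOVA) with the change in total Y-BOCS scores at week 12", and that "gender and baseline Y-BOCS scores will be entered as covariates". For the other outcomes it says only that "Analyses of secondary outcomes will be performed in the same manner". It names no further covariate.

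The abstract (Methods) gives a general form for all outcomes, "analysis of covariance with the change in total outcomes scores at week 12", without covariates. It also says that every measure is taken at weeks 0 and 12, so each secondary scale has a recorded baseline.

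The Randomization section describes minimization "ensuring a balance in baseline Y-BOCS scores (Y-BOCS ≥20) and gender". The two covariates of the primary model are therefore also the two minimization factors. For the primary outcome, baseline Y-BOCS is both the outcome's own baseline and a design factor. For a secondary outcome these two roles fall to different variables, and the plan does not say which of them is carried over.

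**The concern.** An analyst who follows the text word for word would fit, for example, week-12 change in PHQ-9 on treatment, gender and baseline Y-BOCS, and could fairly claim to have followed the plan. That model leaves out the baseline that usually predicts the change best, although it has been measured. An analyst who reasons by analogy would put baseline PHQ-9 in place of baseline Y-BOCS and lose a minimization factor. A third could include both.

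All three models fit the sentence. They will generally give different estimates and P values from the same 30 participants, and each secondary comparison is judged at P<.05. With about 15 per arm, chance differences in baseline depression, anxiety or quality of life can be sizeable, and minimization does not act on those scales directly. At stake are the precision of the secondary results and a choice of model that could still be made after the data are seen.

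**Working it through.** The plan gives no figure for the secondary-outcome model, so there is none to reproduce. The check compares the literal model with own-baseline ANCOVA.

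**Inputs from the document.** Fifteen participants per group (abstract, Methods); response is change at week 12; named covariates are gender and baseline Y-BOCS.

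**Assumptions, not in the document.**
- *r*: correlation of a secondary scale's baseline with its week-12 value, 0.3 to 0.7.
- *q*: correlation of that baseline with baseline Y-BOCS, 0 to 0.5.
- Equal SDs at both visits.
- Baseline Y-BOCS relates to the week-12 value only through the scale's own baseline (correlation *rq*).

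**Residual variance, in units of the scale's SD squared.**
- Change adjusted for baseline Y-BOCS only: 2(1 − r) − q²(1 − r)².
- Change adjusted for own baseline: 1 − r².

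| r | q | Y-BOCS only | Own baseline | Variance ratio | SE ratio |
|---|---|---|---|---|---|
| 0.3 | 0 | 1.400 | 0.910 | 1.54 | 1.24 |
| 0.3 | 0.5 | 1.277 | 0.910 | 1.40 | 1.185 |
| 0.5 | 0 | 1.000 | 0.750 | 1.33 | 1.155 |
| 0.5 | 0.3 | 0.978 | 0.750 | 1.30 | 1.142 |
| 0.5 | 0.5 | 0.938 | 0.750 | 1.25 | 1.118 |
| 0.7 | 0 | 0.600 | 0.510 | 1.18 | 1.085 |
| 0.7 | 0.5 | 0.578 | 0.510 | 1.13 | 1.064 |

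The variance ratio runs from 1.13 to 1.54, and the standard error is 6% to 24% larger. Even at q = 0.5, adjusting for Y-BOCS recovers only part of the loss.

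**Effect of a chance baseline imbalance.** Let the arms differ by D at baseline on the secondary scale, with Y-BOCS balanced. The expected week-12 difference is the treatment effect plus rD. The change score subtracts D, so the contrast is the treatment effect minus (1 − r)D. The imbalance is therefore over-corrected by (1 − r), not ignored.

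With 15 per arm, one standard error of D is √(2/15) = 0.365 SD. At r = 0.5 the shift is 0.5 × 0.365 = 0.18 SD. At r = 0.3 it is 0.7 × 0.365 = 0.26 SD, and at r = 0.7 it is 0.3 × 0.365 = 0.11 SD. These are shifts for a one-SE imbalance in one trial. Over repeated randomizations D averages zero, so there is no systematic bias.

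**The two effects are one.** The excess variance is 2(1 − r) − q²(1 − r)² − (1 − r²) = (1 − r)²(1 − q²). That is the scatter produced by the over-correction, so the precision loss and the shift should not be added together.

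**Cost of the fuller model.** With 30 participants and treatment, gender, baseline Y-BOCS and an intercept, 30 − 4 = 26 residual degrees of freedom remain. Adding own baseline leaves 25.

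**The case against.** The strongest objection is that the sentence need not mean adjustment for Y-BOCS alone. The primary model adjusts an outcome for its own baseline, so the same manner can naturally mean own baseline for each secondary scale. The sentence cannot be applied word for word in any case: the response in the primary model is change in Y-BOCS, and every reader has to substitute the secondary scale there. Under this reading the precision loss calculated above is nil. This stands. A reader might infer that the plan has chosen Y-BOCS adjustment over own-baseline adjustment, but the document does not say so.

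A reader might also infer that baseline imbalance goes uncorrected or biases the secondary results. That does not hold either. A change score already subtracts the own baseline with slope 1, and the estimate is unbiased over randomizations.

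A further objection is that a journal article may leave covariate lists to a full analysis plan. It has some force and is a reason to rate the point as minor. But the article does name covariates and does extend that model to the secondary outcomes, so the difficulty lies in what it fixes rather than in what it omits.

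The size also rests on assumed correlations. The upper end (1.54) needs a low r and no link with Y-BOCS. It is least plausible for the OCI, which measures obsessive-compulsive symptoms and may track Y-BOCS closely.

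Finally, a blanket own-baseline rule would not suit the WAI-SF. It measures the bond between therapist and participant, a week-0 score precedes any ICBT contact, and the usual-care arm has no ICBT therapist.

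**Conclusion.** The point holds as a minor one, for secondary outcomes only. The sentence admits at least two models, and neither is ideal: the literal one omits each scale's own baseline, and the analogous one drops a minimization factor. If the literal model is fitted, the standard error is about 6% to 24% larger than with own-baseline ANCOVA, for r from 0.3 to 0.7 and q from 0 to 0.5. A one-SE chance imbalance then moves the contrast by about 0.18 SD at r = 0.5. If the analogous model is fitted, that loss does not arise. The only gap is then the dropped design factor, whose effect cannot be sized from the document.

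The primary Y-BOCS analysis already adjusts for its own baseline, so neither it nor the sample size is touched.

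**What to change.** Replace the sentence on secondary outcomes with wording such as: *For the OCI, BAI, PHQ-9, GAD-7 and EQ-5D, the week-12 change will be analysed by ANCOVA with treatment, gender, the baseline value of that outcome and baseline Y-BOCS as covariates.* Add a separate sentence giving the rule for the WAI-SF, including whether its week-0 value is used and whether the arms are compared on it at all.

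This improves the model on either reading: it adds own baseline if that was left out, and it keeps the minimization factor if that was swapped out. It should be fixed before outcome data are examined. The cost is a sentence for these five scales, a short rule for the WAI-SF and one degree of freedom per model, with no new data.

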### Ethics and Dissemination

This study will be conducted at the Academic Outpatient Clinics of Chiba University and Fukui University in Japan. When potential participants contact the study trial office through the Chiba University, they will be informed of the study objectives and be asked if they are willing to participate by phone screening. Each participant will then be required to provide written informed consent for their participation in this study. Each participant will be informed that all participants will receive UC from their general practitioner and that half of the recruited participants will also receive ICBT in addition to their UC. All adverse events will be reported, and serious adverse events will be immediately reported to the Institutional Review Board of Chiba University Hospital in addition to being registered with the hospital risk management system. An adverse event will be defined as a symptom or disease occurring during the clinical trial, whether related to the ICBT program or not. The study will be conducted and reported according to CONSORT-ETHICS guideline recommendations [39].

This clinical trial protocol was approved by the clinical trial review committee of Chiba University Hospital on November 18, 2019 (G2019017) and approved by the ethics review committee of the Fukui University Graduate School (20190075). It is registered in the University Hospital Medical Information Network database of clinical trials in Japan (UMIN: 000044422).

## Results

The study period is from January 6, 2020 to March 31, 2021. The case registration period is scheduled for 12 months from January 6, 2020 to December 31, 2020.

## Discussion

This randomized controlled study will evaluate the effectiveness of ICBT for patients with OCD. The findings of this study will provide valuable evidence to facilitate development and establish treatment algorithms in ICBT for patients with OCD. The study will also introduce this method for providing ICBT in Japan, as patients will be given access to self-help materials using an e-learning system (LearningBox) and medical chat app (MediLine). The UC control group will be randomly assigned, and the multicenter study design will reduce bias and improve the likelihood of obtaining generalizable results. The study will also have limitations, including the inability to elucidate the specific effects of ICBT program because there is no placebo group to control for nonspecific factors. The study also will not control for medical therapies or treatment resistance. It is unclear whether pharmacotherapy plus CBT improves OCD symptoms more than pharmacotherapy alone [4,40]. Therefore, combination therapy with pharmaceuticals and ICBT should be tested in future trials to determine whether each is beneficial or if therapy is improved by combined therapies.

## Appendix

Multimedia Appendix 1 LearningBox E-Learning System.

Multimedia Appendix 2 The MediLine Chat App.

## Abbreviations

BAI: Beak Anxiety Inventory
CBT: Cognitive Behavioral Therapy
EQ-5D: EuroQol-5-Divison
GAD-7: Generalized Anxiety Disorder-7
ICBT: Internet-Based Cognitive Behavioral Therapy
JART: Japanese Adult Rating Test
OCD: Obsessive-Compulsive Disorder
PHQ-9: Patient Health Questionnaire-9
RCT: Randomized Controlled Trial
UC: Usual care
WAI-SF: Working Alliance Inventory-Short From
Y-BOCS: Yale-Brown Obsessive-Compulsive Scale
